### Statistical Analysis

All patients who have been randomized and have received an injection will be included in the statistical evaluation. Statistical tests will be performed and reported according to the intention-to-treat principle. Data will be presented as mean and standard deviation or median and range, as appropriate, for continuous variables and as numbers and proportions for categorical variables. The primary analysis of the CTS symptom severity score at 10 weeks will be performed using a mixed model analysis of repeated measures (baseline, 5 weeks, 10 weeks) with treatment effect (placebo or Methylprednisolone) and time as fixed factors in a first step and with the interaction term of treatment and time in second step. The results will be presented as differences in mean score change over time (baseline to 10 weeks) and 95% confidence intervals. The secondary analysis of the symptom severity score will be done using a mixed model with treatment (placebo or Methylprednisolone) as a random factor and time (baseline, 5 weeks, 10 weeks, 24 weeks, 52 weeks) as fixed factor and surgery as covariate; first step without interaction terms and second step with two-way interaction of treatment and time. The results will be presented as differences in mean score change over time and 95% confidence intervals.

The primary analysis of rate of surgery will be done using Fisher's exact test (univariate) and logistic regression (multivariate) with adjustment for baseline variables. The issue of multiplicity is addressed by performing the analysis in the following priority; 52 weeks, 24 weeks, and 12 weeks. The results will be presented as differences in the rate of surgery between the groups (Methylprednisolone compared with placebo) and as adjusted odds ratio (and 95% confidence interval) of having surgery at each time point. The possible dose-response relationship with higher effect of high dose will be explored by prioritizing group comparisons. We will conduct the following predefined subgroup analyses; symptom duration (12 months or shorter versus more than 12 months), symptom severity (baseline symptom severity score below 3.0 versus 3.0 or higher), and median nerve conduction abnormality (moderate or severe versus mild or normal).

Analysis of the secondary end-points will be done with mixed models adjusting for baseline variables. We will also calculate the effect size for the symptom and function scales [20]. The AEs will be reported in table form and stratified in 4 groups according to severity; statistical comparison will be done when appropriate. When at least 60 patients have completed the 24-week visit the frequency of SAEs and of AEs with persistent symptoms will be calculated and the results will be reported and discussed with the Swedish Medical Products Agency.

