## Background

Carpal tunnel syndrome (CTS) is the most common peripheral compression neuropathy in the upper extremity with a prevalence of 3.7% in the adult general population [1]. The prevalence of persons who have moderate or severe CTS but have not sought care or been diagnosed correctly is almost 1% in the general population [2]. CTS of mild severity is commonly treated with wrist splint but for moderately severe symptoms surgical treatment is often required [3]. Carpal tunnel release is one of the most common surgical procedures; the annual incidence in a US population (2001-2005) was 134 per 100,000 [4]

Although carpal tunnel release has been shown to produce good outcomes regarding relief of symptoms caused by CTS [5], it has several disadvantages including surgery-related pain and hand weakness [6]. These are common problems and may last several months after surgery. Other less common complications include wound infection, chronic regional pain syndrome, and nerve injuries [7,8]. In addition, surgery is associated with direct costs as well as indirect costs related to work absence after surgery because the majority of patients require sick leave for a varying length of time depending on the degree of postoperative morbidity and the type of work [9]. The median time of work absence has been 4 weeks in several studies, with a proportion of patients having long-term work disability [9]. The economic impact of work absence following surgery for CTS can be substantial both for the patients and the society. Consequently avoiding sick leave would be an important advantage for nonsurgical treatment.

Although many alternatives to surgery have been proposed there is little evidence to support the efficacy of most of these treatments [10]. Steroid injection into or proximal to the carpal tunnel is widely practiced in the treatment of patients with idiopathic CTS particularly in the United States [11]. However, the evidence for its efficacy beyond one month has not been established in placebo-controlled trials. In a recent Cochrane review of local corticosteroid injection for CTS, the authors concluded that there was evidence supporting clinical improvement at one month compared to placebo but no significant improvement after 8 weeks compared to nonsteroidal anti-inflammatory drugs or wrist splint [12]. None of the studies reviewed involved a double-blind comparison with a follow-up of more than one month.

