### Sample Size

Based on previous studies of surgical outcome in patients with idiopathic CTS the mean improvement in the CTS symptom severity scale at 12 weeks after surgery is about 1.6 (on the 1 to 5 point scale). A mean improvement of less than 0.8 in the CTS symptom severity score cannot warrant recommending steroid injection as an effective alternative treatment. With 90% statistical power, 5% significance level, and two-sided statistical tests, and assuming a standard deviation of 1.0 for the CTS symptom severity score the study can detect a true difference of at least 0.8 point on the CTS symptom severity score between an intervention group and the placebo group when 102 patients have been randomized. The aim will be to enroll 120 patients in the study to account for potential incomplete follow-ups.

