### Primary endpoint

1. The CTS symptom severity score change at 10 weeks after treatment:

1) 80 mg Methylprednisolone vs. placebo

2) 40 mg Methylprednisolone vs. placebo

3) 80 mg Methylprednisolone vs. 40 mg Methylprednisolone

2. The rate of surgery at (in rank order) 52 weeks, 24 weeks, and 12 weeks after treatment:

1) 80 mg Methylprednisolone vs. placebo

2) 40 mg Methylprednisolone vs. placebo

3) 80 mg Methylprednisolone vs. 40 mg Methylprednisolone

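### The first step of the primary symptom model does not estimate the 10-week change, and the plan does not tie the primary test to the second-step contrast that does

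*Protocol article*

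**What the plan says.** Under Primary endpoint, the first item is "The CTS symptom severity score change at 10 weeks after treatment", with three pairwise comparisons in rank order: 80 mg against placebo, 40 mg against placebo, and 80 mg against 40 mg.

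Under Statistical Analysis, this score is analysed over three visits, so baseline is itself one of the outcome values. The model is built up in two stages, entering treatment alongside "time as fixed factors in a first step and with the interaction term of treatment and time in second step". Both stages fall under the primary analysis. What will be reported is then stated separately: "The results will be presented as differences in mean score change over time (baseline to 10 weeks) and 95% confidence intervals".

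The secondary symptom model extends to 24 and 52 weeks and repeats the scheme: "first step without interaction terms and second step with two-way interaction of treatment and time".

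The Background explains why the time point matters. It cites a systematic review which concluded that "there was evidence supporting clinical improvement at one month compared to placebo", and it says that efficacy beyond one month has not been established in placebo-controlled trials.

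**The concern.** A model with treatment and time but no interaction assumes the same group difference at every visit. With baseline in the outcome vector, that common difference is pulled toward the zero expected at baseline. The first step therefore targets a different quantity from the endpoint, and a smaller one if the effect lasts.

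The second step offers two readings. One is the single contrast for change from baseline to 10 weeks, which is the endpoint. The other is the overall treatment-by-time test, which asks whether the arms differ in change at 5 weeks or at 10 weeks. The text does not say which of the three candidate quantities decides the endpoint.

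The stake is specific to this trial. Benefit at about one month is what the Background already regards as supported, and benefit beyond that is the open question. A test that can be significant because of the 5-week visit alone could be read as an answer to that question when it is not.

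**Working it through.** **Inputs from the protocol article (Sample Size):** effect 0.8, SD 1.0, two-sided 5%, 90% power, 102 patients needed, 120 to be enrolled.

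**Assumptions, not in the document:** equal allocation (34 per arm for 102, 40 for 120); SD 1.0 at each visit; compound symmetry with correlation ρ from 0.3 to 0.7; one active arm against placebo; normal theory.

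**1. The plan's own figure.** n per arm = 2 × (1.960 + 1.282)² × 1.0² / 0.8² = 32.8, so 33 per arm and 99 in total. With the exact noncentral t, 33 per arm gives 89.3% and 34 gives 90.2%; 34 × 3 = 102. The sample size reproduces and is not affected by this point.

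**2. What step one estimates.** Write the true group differences as (0, d5, d10). Under compound symmetry with complete data the three visits get equal weight, so the treatment coefficient estimates (0 + d5 + d10)/3, whatever ρ is.
- 0.8 at both follow-ups: (0 + 0.8 + 0.8)/3 = 0.53.
- 0.8 at 5 weeks only: 0.8/3 = 0.27.

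The weights change if baseline is less variable. With an assumed SD of 0.7 at baseline and 1.0 later, correlations of 0.4 between baseline and follow-up and 0.6 between follow-ups, and an unstructured covariance, the weights are 0.712, 0.144 and 0.144. The estimate becomes 0.8 × 0.288 = 0.23. This is one illustrative set of values.

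**3. Step one cannot give the promised result.** If the mean in an arm at visit t is μ + τ·arm + β_t, the arms differ by τ at 10 weeks and by τ at baseline. The difference in change is τ − τ = 0 by construction, whatever the data. A difference in mean change from baseline to 10 weeks can come only from the model with the interaction.

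**4. Rejection rates, 34 per arm.**
- Step one: standard error √[(2/n)(1 + 2ρ)/3].
- 10-week contrast: standard error √[(2/n) × 2(1 − ρ)].
- Overall interaction: 2-df chi-square. For 0.8 at 5 weeks only, the noncentrality is 0.8² × n / [3(1 − ρ)], which at ρ = 0.5 is 0.64 × 34 / 1.5 = 14.5.

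| True effect | Test | ρ = 0.3 | ρ = 0.5 | ρ = 0.7 |
|---|---|---|---|---|
| 0.8 at 5 weeks, 0 at 10 | Overall interaction | 83% | 94% | 99.6% |
| | Step-one treatment effect | 33% | 27% | 23% |
| | 10-week contrast | 5% | 5% | 5% |
| 0.8 at 5 and 10 weeks | Step-one treatment effect | 85% | 77% | 69% |
| | 10-week contrast | 80% | 91% | 99% |

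An F reference in place of the chi-square gives 82%, 93% and 99.5% for the interaction. The three-arm, 4-df version, with both doses acting at 5 weeks only, gives 85%, 95% and 99.8%. With 40 per arm the 2-df F test gives 88%, 96% and 99.9%. A simulation with 40 per arm at ρ = 0.5 (8,000 runs) gave 97% for the interaction, 30% for step one and 5% for the 10-week contrast.

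**5. Secondary model.** The same algebra applies over five visits. A first step without interaction carries one constant group difference over baseline, 5, 10, 24 and 52 weeks, while the secondary endpoint is the change at 52 weeks.

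**The case against.** The strongest reply is that the plan already points to the right quantity. The analysis is introduced as that of the 10-week score, and the results sentence promises the difference in change from baseline to 10 weeks with a 95% interval. Step two contains that contrast, and its interval corresponds to the two-sided 5% test in the Sample Size section. Since step one cannot yield a difference in change, the promised result can come only from step two. A 5-week-only effect would then be exposed, because the reported 10-week interval would exclude zero in only 5% of trials.

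Most of this stands. A reader might infer that neither step tests the 10-week endpoint, or that the overall interaction test is the decision rule. The document supports neither inference: the right contrast is in step two and will be reported, and no overall test is named as a criterion. The 83% to 99.6% therefore describes what would follow if that test were used, not what the plan prescribes.

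A reader might also infer that step one always loses power. It does not: at ρ = 0.3 it has more power than the contrast (85% against 80%). The error in what it estimates remains at any correlation.

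It can also be said that a condensed article may leave the exact contrast to an analysis plan. That would answer a mere omission. Here the article itself fixes a first primary step that targets the wrong quantity, and the results sentence governs presentation without saying which test decides.

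**Conclusion.** The point holds in a limited form. A stated step of the primary analysis does not estimate the primary endpoint and cannot produce the result the plan promises. The contrast that does is available in step two and will be reported, but the primary test is not tied to it. Three quantities that can disagree are left within one primary analysis.

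The size is a true 0.8 shown as 0.53 by step one. That figure needs compound symmetry with equal visit SDs but no particular correlation. The rejection rates additionally need the assumed correlation range and, for the 5-week-only case, a deliberately sharp profile of full effect at 5 weeks and none at 10. Because the endpoint, visit, comparisons and reported interval are all stated and agree, this is a should-fix, not a must-fix.

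**What to change.** In Statistical Analysis, remove the first step from both the primary and the secondary symptom models. Fit one model with arm (three levels, to match the listed comparisons), visit as a categorical factor, and arm-by-visit. State that the primary test and estimate for each ranked comparison is the arm contrast in change from baseline to 10 weeks, with its 95% confidence interval. For the secondary endpoint, name the corresponding 52-week contrast. Add that neither the treatment main effect nor the overall treatment-by-time test is used for inference.

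The cost is wording in one section. No new data or additional patients are needed, and the 102 and 120 figures stay as they are. For a true 0.8 at 10 weeks, the named contrast has power of 80%, 91% and 99% with 34 per arm, and 86%, 95% and 99.6% with 40 per arm, at correlations of 0.3, 0.5 and 0.7.

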## Methods/Design

### Design

The trial is a prospective randomized double-blind placebo-controlled dose-response clinical trial comparing injection of 40 mg Methylprednisolone, 80 mg Methylprednisolone or placebo into the carpal tunnel in patients with moderately severe idiopathic CTS not previously treated with steroid injection.

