### Secondary endpoint

1. The CTS symptom severity score change at 52 weeks

2. Time to surgery

3. The *Quick*DASH score at 10 weeks and 52 weeks

4. The SF-6D score at 10 weeks and 52 weeks

5. Patient satisfaction with treatment at 10 weeks and 52 weeks

6. Duration of sick leave at 52 weeks (for employed patients)

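### The secondary symptom model enters treatment as a random factor, so the promised between-group difference is undefined or, on some readings, shrunk toward zero

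*Protocol article*

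**What the plan says.** The Statistical Analysis section of the protocol article describes two models for the symptom severity score.

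- **Primary model** (baseline, 5 and 10 weeks): a repeated-measures mixed model "with treatment effect (placebo or Methylprednisolone) and time as fixed factors in a first step", with their interaction added in a second step.
- **Secondary model** (baseline to 52 weeks): a "mixed model with treatment (placebo or Methylprednisolone) as a random factor", with "time (baseline, 5 weeks, 10 weeks, 24 weeks, 52 weeks) as fixed factor and surgery as covariate". It too is fitted in two steps: "first step without interaction terms and second step with two-way interaction of treatment and time". The text does not say whether that interaction is fixed or random.

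For the secondary model the stated output is: "The results will be presented as differences in mean score change over time and 95% confidence intervals".

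This model serves the first item under Secondary endpoint, "The CTS symptom severity score change at 52 weeks". The Design section describes a trial "comparing injection of 40 mg Methylprednisolone, 80 mg Methylprednisolone or placebo into the carpal tunnel". Nothing else in the article explains or corrects the change of treatment from fixed to random.

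**The concern.** A factor is treated as random when its levels stand for a wider population and the spread of that population is of interest. Here the levels are two specified doses and placebo, and the parameter of interest is the difference between them. Making treatment random replaces that difference with a variance, estimated from two or three levels and so on 1 or 2 degrees of freedom. Arm effects are then available only as predictions, which are pulled toward the common mean. When the variance estimate is zero, all the predicted differences are zero.

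At stake is the 52-week symptom comparison. The Background presents lasting benefit beyond one month as the open question, so this secondary result carries weight. An analyst who follows the text has no ordinary contrast to report. One who quietly makes treatment fixed departs from the published plan.

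**Working it through.** **1. The plan's own figure.** Inputs from Sample Size: difference 0.8, SD 1.0, two-sided 5%, power 90%. The normal formula gives n = 2(1.960 + 1.282)² × 1.0² / 0.8² = 32.8, so 33 per arm. With the noncentral t, 33 per arm gives 89.3% power and 34 gives 90.2%. Three arms of 34 make 102, as stated. The sample size is not in question.

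**2. What the secondary model contains.**

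| Step | Fixed part as written | Source of a group difference |
|---|---|---|
| 1, no interaction | intercept, time, surgery | predicted treatment effects only |
| 2, with treatment-by-time | the same, plus the interaction only if it is coded fixed | predictions if the interaction is random; ordinary contrasts in change if it is fixed |

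A difference in change has to come from the interaction. By convention an interaction with a random factor is itself random, but the text does not settle this.

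**3. Size of the shrinkage if differences are read as predictions.** The layout is simplified to a one-way comparison at one time point with SD 1.0. Equal allocation is assumed, which makes 40 per arm at the enrolment target of 120.

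- Three levels, balanced: predicted difference = d × max(0, 1 − MSW/MSB), where d is the observed difference and MSW and MSB are the within-arm and between-arm mean squares.
- Two levels: predicted difference = d × max(0, 1 − v/d²), with v = s²(1/n₁ + 1/n₂), where s² is the within-group variance.

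Averages over 200,000 simulated trials per row:

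| Layout | True difference | Mean predicted | Variance estimated as zero |
|---|---|---|---|
| 3 levels, 40 per arm, both doses 0.8 | 0.8 | 0.708 | 0.2% |
| 3 levels, 40 per arm, doses 0.8 and 0.4 | 0.8 | 0.676 | 0.9% |
| 3 levels, 40 per arm, both doses 0.4 | 0.4 | 0.258 | 16.8% |
| 3 levels, 34 per arm, both doses 0.8 | 0.8 | 0.690 | 0.5% |
| 3 levels, 34 per arm, both doses 0.4 | 0.4 | 0.248 | 20.6% |
| 2 levels, 40 v 80 | 0.8 | 0.749 | 0.1% |
| 2 levels, 40 v 80 | 0.4 | 0.307 | 14.2% |

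Hand check of the two-level rows: v = 1/40 + 1/80 = 0.0375. For d = 0.8, 0.8 × (1 − 0.0375/0.64) = 0.753. For d = 0.4, 0.4 × (1 − 0.0375/0.16) = 0.306. Both agree with the simulated means.

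At 40 per arm with three levels and equal doses, the loss is 1 − 0.708/0.8 = 12% for a true 0.8 and 1 − 0.258/0.4 = 36% for a true 0.4. With two levels it is 1 − 0.749/0.8 = 6% and 1 − 0.307/0.4 = 23%.

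**4. One simulated five-visit data set** (120 patients, three arms, first-step model without the surgery covariate). With treatment random, the fixed part held only the intercept and time. Treatment appeared as one variance, 0.113, and the predicted differences from placebo were −0.48 and −0.60. With treatment fixed, the same data gave −0.54 (95% CI −0.87 to −0.21) and −0.67 (95% CI −1.00 to −0.34). This shows what each coding returns; it is not a forecast for the trial.

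**The case against.** The best defence is that the phrase is a slip, perhaps for patient as the random factor. Both models promise the same kind of result, and the primary model has treatment fixed. That is plausible, but the text cannot confirm it, and the role of treatment is stated outright rather than left to a fuller document.

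The second objection is stronger. A reader might infer that the 24- and 52-week differences will be biased toward no effect. The article does not support so firm a conclusion. Shrinkage arises only if differences are taken from predicted effects or the interaction is random. If the second-step interaction were coded fixed, unshrunken contrasts in change with confidence intervals would be available. This part of the objection stands, and the claim of bias has to remain conditional.

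Three further limits also stand.

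- A reader might fault the plan for not naming the patient as the random effect. An article may leave that to the full plan, and the primary model does not name it either.
- A calculation with two equal groups of 34 gives 0.72 for a true 0.8 and 0.28 for a true 0.4, with zero variance in 25% of trials at 0.4. The trial has no such layout; pooling the steroid arms gives about 40 v 80.
- A score difference at 24 weeks is not a listed endpoint. Of the listed endpoints, the wording bears on the 52-week score change.

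**Conclusion.** The specification is wrong as written and should be corrected. Treatment is random in a model meant to deliver a contrast between chosen arms, and the article does not establish how that contrast and its interval would be obtained.

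If differences are read as predictions, a true 0.8 is reported on average as roughly 0.71 (three levels, doses equally effective) or 0.75 (two levels), and a true 0.4 as roughly 0.26 or 0.31. At a true 0.4 the reported difference is exactly zero in about 17% or 14% of trials. These figures assume SD 1.0, equal allocation at 40 per arm and a single time point. They leave out the baseline score, repeated measures and the surgery covariate, so they indicate scale only. The smaller effect of 0.4 is an illustrative value, not one taken from the article.

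The scope is limited to this secondary analysis. A reader might suppose that the main results are compromised too, but the primary 10-week model has treatment fixed, and the surgery rate is analysed by Fisher's exact test and logistic regression. For that reason this is a should-fix point.

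**What to change.** Reword the secondary model so that treatment (three levels), time and treatment-by-time are all fixed effects, with within-patient correlation handled as in the primary repeated-measures model. State that the fixed contrasts in change from baseline at 52 weeks, and at 24 weeks, will be reported with 95% confidence intervals. This costs one sentence in the Statistical Analysis section and needs no new data, no change of design and no change to the sample size.

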### Follow-up

At the *Baseline *visit, demographics, earlier and ongoing disease, and concomitant medication are recorded. The baseline data include weight, height, and smoking and employment status. The patient completes a questionnaire that includes demographic data, the CTS symptoms severity scale, the 11-item disabilities of the arm, shoulder and hand (*Quick*DASH) questionnaire, and the SF-6D. A physical examination is performed.

At *5 weeks *after injection a telephone interview is conducted by the investigator and the patient is asked to complete the CTS symptoms severity scale and concomitant medication and adverse events (AEs) will be recorded.

At *10 weeks *after injection the patient is examined by the physical therapist. The investigator asks the patient whether she/he wants to proceed with surgery as planned at 12 weeks after injection or whether the patient has experienced adequate symptom relief that she/he wants to continue follow-up and not have the planned surgery at this stage. An evaluation similar to the baseline evaluation is performed and the indication for surgery is recorded. The patient completes the CTS symptoms severity scale. Concomitant medication and AEs are recorded. Possible use of a wrist splint since the injection and its frequency is recorded.

At 12 weeks the patient who had chosen to have surgery is operated on as scheduled.

At *24 weeks *after injection the patient is examined and asked to complete a questionnaire including the CTS symptoms severity scale, *Quick*DASH, and the SF-6D as well as to rate satisfaction with the treatment on a visual analog scale from 0 (very dissatisfied) to 100 (completely satisfied). Concomitant medication and AEs are recorded.

At *52 weeks *after injection the patient is asked to attend a physical examination and nerve conduction tests and complete the questionnaires.

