### Blinding

The nurse at the outpatient clinic prepares the medication with a label covering the syringe. The injection will then be administered to the patient by the investigator. The placebo is clear and Methylprednisolone is a white suspension. In subfascial injections such as in the carpal canal leakage from the injection canal is small. The investigator administering the injection presses a medical dressing over the puncture site while withdrawing the needle; this will conceal the color in case of leakage. The decision whether or not to have surgery is done by the patient at 10 weeks and the patients are instructed to make that choice based on their symptoms and functional status at that time. At the 24-week and 52-week patient visits the palm is covered by a bandage with a dressing to blind the examining physical therapist as to whether the patient had undergone surgery after the injection. All follow-up evaluations are done by a physical therapist blinded to the group assignment.

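### The symptom-score model to 52 weeks adjusts for surgery, a post-randomisation event chosen on the treatment response, and no target is named for the adjusted effect

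*Protocol article*

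**What the plan says.** Under Statistical Analysis, the protocol article describes two symptom-score models. The primary one uses baseline, 5 and 10 weeks and does not mention surgery. The secondary one adds 24 and 52 weeks, with time "as fixed factor and surgery as covariate; first step without interaction terms" and a treatment-by-time interaction in a second step. It serves the first-listed secondary endpoint, "The CTS symptom severity score change at 52 weeks".

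The same section states: "Statistical tests will be performed and reported according to the intention-to-treat principle". Its closing part says that secondary endpoints are analysed by mixed models with adjustment for baseline variables.

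Follow-up describes how surgery comes about. At the 10-week visit, "The investigator asks the patient whether she/he wants to proceed with surgery as planned at 12 weeks after injection" or continue without it; then "At 12 weeks the patient who had chosen to have surgery is operated on as scheduled". Blinding adds that "patients are instructed to make that choice based on their symptoms and functional status at that time". Primary endpoint 2 is "The rate of surgery at (in rank order) 52 weeks, 24 weeks, and 12 weeks after treatment".

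**The concern.** Surgery follows randomisation and depends on the 10-week response, which is what the injection is meant to alter. The protocol itself counts it as an outcome. It also acts strongly on the score being modelled: Sample Size cites a mean improvement of about 1.6 points after surgery, against a target difference of 0.8.

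Once such a variable is held fixed, steroid and placebo patients are compared within operated and within unoperated groups, which were selected differently in the two arms. The treatment coefficient is then not the effect of assignment. Nor is it in general the effect that would be seen without surgery. The Discussion accepts that the option of surgery may influence the results but names no quantity for the adjusted model to estimate. At stake is how the 24- and 52-week symptom results are interpreted.

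**Working it through.** **Stated figures.** The plan gives no figure for this model. Its sample size supplies the scale: difference 0.8, SD 1.0, two-sided 5%. An exact two-sample t-test with 34 per arm has power 90.2%, and 3 × 34 = 102, as stated. Omitting surgery does not change that number.

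**Assumed inputs.** The article gives no expected surgery rates and no course of drug benefit after 10 weeks. Treatment is taken as a fixed effect, with two arms and complete data. Let
- p_C and p_T be the surgery proportions on placebo and steroid;
- g be the 52-week gain from surgery relative to an unoperated placebo patient;
- d be the drug benefit still present at 52 weeks in unoperated steroid patients, assumed to add nothing in operated patients.

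Negative contrasts favour steroid.

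**Contrast without surgery in the model (randomised comparison):** g(p_C − p_T) − d(1 − p_T).

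**Contrast with surgery as a time-varying covariate.** With no treatment-by-surgery term, the coefficient is approximately a weighted average of the difference among operated patients (0) and among unoperated patients (−d):
- w_O = p_T·p_C / (p_T + p_C)
- w_U = (1 − p_T)(1 − p_C) / [(1 − p_T) + (1 − p_C)]
- adjusted contrast = −d·w_U / (w_U + w_O)

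**Numbers for 70% vs 47%, g = 1.2.** w_O = 0.47 × 0.70 / 1.17 = 0.281; w_U = 0.53 × 0.30 / 0.83 = 0.192; weight on the unoperated = 0.192 / 0.473 = 0.405. The last column is a simulated five-visit random-intercept model with 3000 patients per arm.

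| d (true no-surgery effect = −d) | Randomised contrast | Adjusted contrast | Shift | Simulated: without → with surgery |
|---|---|---|---|---|
| 0 | 1.2 × 0.23 = +0.28 | 0 | 0.28 | +0.29 → +0.01 |
| 0.4 | 0.276 − 0.4 × 0.53 = +0.06 | −0.4 × 0.405 = −0.16 | 0.23 | +0.10 → −0.14 |
| 0.8 | 0.276 − 0.8 × 0.53 = −0.15 | −0.8 × 0.405 = −0.32 | 0.18 | −0.16 → −0.33 |

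**Other assumed rates** (g = 1.3, that is 1.6 from baseline less 0.3 improvement without surgery; 6000 simulated per arm):
- 70% vs 55%: +0.18 → 0.00 (d = 0), 0.00 → −0.15 (d = 0.4), −0.18 → −0.30 (d = 0.8). Shifts 0.12 to 0.18.
- 64% vs 42%: +0.29 → 0.00 (d = 0), −0.18 → −0.38 (d = 0.8). Shifts 0.29 and 0.20.

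The adjusted model finds the no-surgery effect when d = 0 and misses it when benefit persists: about −0.15 against −0.4, and −0.30 to −0.38 against −0.8. By the same weighting it would also find it if the benefit were equal in operated and unoperated patients.

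**Constant ever/never coding.** A covariate that is constant within a patient carries no information on within-patient change when all visits are present. The step-two treatment-by-52-week contrast was identical with and without it. The step-one treatment effect, which averages over visits, did move: −0.30 to −0.20 at 70% vs 47%, and −0.40 to −0.32 at 64% vs 42% with d = 0.8. At 70% vs 55% it moved by at most 0.02.

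**The case against.** The best defence is that the harm depends on details the article does not fix. Coding is ordinary analysis-plan detail. Under constant coding with complete data, the step-two change contrast, the natural reading of the promised differences in score change, is untouched. Under time-varying coding nothing is attributed to surgery before it happens. Nobody is excluded or moved between groups, so intention to treat is kept in the narrow sense. A comparison that ignores surgery has its own weakness, since it mixes in surgical benefit in both arms.

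Much of this stands, and it limits what can be claimed. A reader might infer four stronger points that the document does not support.

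- **A demonstrated false-positive inflation.** Regressing the 52-week score alone on treatment and surgery, in a scenario with no direct drug effect at 52 weeks, gave +0.15 and rejected in 11% of simulated trials. That is not the planned model. With the same inputs over five visits, the contrast was +0.164 both without surgery and with constant coding, and −0.03 with 4.8% rejection under time-varying coding. Repeated pre-surgery scores carry the persistent severity that the single-visit regression omits.
- **A surgery effect assigned to baseline, 5 and 10 weeks.** This is true only of constant coding, which the article does not state.
- **The whole one-year efficacy claim rests on this model.** The 52-week surgery rate is a primary endpoint, analysed by Fisher's test and logistic regression with baseline adjustment. The 10-week primary symptom model precedes surgery.
- **QuickDASH and SF-6D share the fault.** They are to be adjusted for baseline variables, with no mention of surgery.

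What the defence does not answer is that surgery is named as a covariate without a target. The open coding allows materially different 52-week answers, and no coding gives a clear reason to have the covariate in the main model.

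**Conclusion.** The point holds for the symptom-score analysis at 24 and 52 weeks. The adjustment conditions on a consequence of treatment, departs from two principles stated in the same section, and estimates nothing the document defines.

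At assumed surgery rates of about 70% vs 47%, time-varying coding moves the 52-week contrast by about 0.2 to 0.3 points, enough to change its sign in one scenario. Constant coding leaves the step-two contrast unchanged and shifts the step-one effect by about 0.1. These sizes rest on assumed rates, an assumed gain from surgery, drug benefit confined to unoperated patients, complete data and treatment as a fixed effect. They illustrate the problem and do not predict the trial's result. Neither the size nor the direction of any distortion can be fixed from the article. Because one secondary endpoint is affected, this is a should-fix.

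**What to change.** In Statistical Analysis, remove surgery from the main symptom-score model to 52 weeks. State that this analysis compares the groups as randomised whether or not surgery took place (a treatment-policy estimand) and is to be read beside the surgery rate. Any analysis that handles surgery can stay as supplementary, provided its estimand, the coding of surgery and its assumptions are written down beforehand.

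The 10-week primary symptom analysis, the surgery-rate analysis, QuickDASH and SF-6D need no change on this ground.

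The cost is wording only, and the sample size is unaffected. The downside is that the main comparison includes the benefit of surgery in both arms. It may show little difference at 52 weeks, or favour placebo if more placebo patients are operated on, as in the first row of the table. This is why it must be reported with the surgery rate.
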